#### Procedures for the Standard group

After an introduction to the MDB system and the Fitbit bracelet, participants will enter data into the system daily in a four-week period. Participants will receive a weekly telephone call from the investigator evaluating (a) experience with the MDB system, (b) suicidal ideations, (c) side effects of medications, (d) worsening of depression, and (e) compliance with data entry. Patients will be reminded to contact either the IOS or the psychiatric emergency unit if they experience aggravation in depressive symptoms.

#### Procedures for the CRT group

Participants in the *CRT group* will enter data into the MDB system, as in the standard group, but an extra module is added to the system, using a graphical depiction of a manometer measuring day-to-day variation in sleep onset, and another manometer measuring changes in sleep midpoint. The manometers serve as a psychoeducational tool for the patients to spot and adjust changes in their sleep timing.

The CRT intervention also includes an individual CRT psychoeducational session at baseline and in one of the next two subsequent days, and with booster sessions at the weekly telephone calls. The initial two CRT sessions are provided by the investigator as an individual 1-h session including an introduction to the CRT principles using a full written CRT guide, and a leaflet version, focusing on how participants can incorporate adequate and timed zeitgeber stimuli into their daytime activities regarding daylight exposure, exercise, meals, and social contact. The investigator then helps the participant to fill in a schedule called “basic strategy for daily structure” and provides the participant with a paper and pen diary “The Chrono schedule” where the daily timing of daylight exposure, exercise, meals, and social contact must be noted for the morning, afternoon and evening time-period (see Fig. 2). Finally, the investigator helps the participant to formulate and write down three problems, within the CRT area, they want to work with, in the following 4 weeks, for example: how to achieve an earlier bedtime, how to achieve more daylight, and how to achieve more regular meals.

**Fig. 2 Fig2:**
[figure not shown]
The Chrono schedule used to implement Circadian Reinforcement Therapy (CRT). Patients register daily timing of meals, social interaction, exercise and daylight exposure

The Fitbit will be set to a goal of 4000 steps, alerting with a vibration when this is reached, to nudge participants to be more active.

The weekly telephone calls will cover the same elements as in the *Standard group*, supplemented with a discussion of management of the three identified problems, patterns in the Chrono schedule, and in the graphical representation of self-monitored data. This will enable a discussion on how to strengthen zeitgeber stimuli and advance the sleep period and point out any patterns in the graphical display between for example delayed sleep and mood worsening.

Participants’ data registrations, in the MDB system, will be evaluated daily (Monday to Friday) by the investigator. Patients will be contacted if data is missing or if the registrations show predefined trigger signs of aggravation of depression or unstable sleep patterns (described in Table 1).

**Table 1 Tab1:** Triggers for clinicians telephone call based on inspecting of daily self-assessments in the Monsenso Daybuilder system

Parameter	Evaluation criteria for feedback
Sleep (one of these)	✓More than 10 or less than 4 h sleep a night
	✓A drop-in sleep quality of 4 or above (from 8 to 4 e.g.)
	✓Variation of 3 h or more between two adjoining days in wake-up time or sleep onset
	✓More than 3 awakenings a night for two nights
	✓Late sleep for 3 days – with sleep onset after midnight and wake up time after 9 am
Depression severity (on of these)	✓Drop in daily depression score of 3 or more (e.g. from 8 to 5)
	✓A daily depression score of 2 or less
	✓Morning depression score of 2 or less
Medication	✓More than 1 day without medication registration
Activity	✓More than 1 day without activity registration

#### Concomitant care

All participants will be following the standard IOS treatment program as described above.

### Outcomes

#### Diagnostic measures

The Mini International Neuropsychiatric Interview (M.I.N.I.) 4.0 (Danish version) is used for diagnosis. This is a short, structured diagnostic interview based on the DSM-IV diagnostic system, and will be conducted to confirm depression diagnosis, assess comorbidity, and any contraindications for participation in the trial [49]. Investigators are certified in the use of the M.I.N.I. instrument.

#### Psychometrics and sociodemographics

Sociodemographic data are collected at baseline together with a treatment outcome expectancy rating. Psychometric assessments are performed at baseline and at the endpoint visit. Rating window is set as last 3 days for all instruments except for the Pittsburgh Sleep Quality Index (PSQI) that covers the last month. The severity of depression is assessed by the Hamilton Depression Rating scale, 17 item version, which includes the core symptoms of depression (HAM-D_6_), and the Bech-Rafaelsen Melancholia Rating Scale (MES) focusing more on the cognitive symptoms of depression [50, 51]. The Hamilton rater is blinded to treatment allocation and is trained in the use of the HAM-D_17_ by repeated groups ratings with co-researchers. Self-assessed depression severity is measured by the Major Depression Inventory (MDI), a 10-item questionnaire covering both the ICD-10 and the DSM-IV diagnostic criteria for depression [52]. The response categories of each item are from “at no time” (0) to “all the time” [5], with a score range from 0 (zero) to 50 and a cut-off score of 21 for mild depression, 26 for moderate depression and 31 for severe depression. The WHO-5 Wellbeing index is used as a measure of Quality of life [53]. The WHO-5 consist of 5 items, each rated from “all of the time” (5) to “at no time” (0). The raw score is calculated by summing items multiplicated by four, giving a score range from 0 to 100, where 0 is worst possible and 100 is the best possible quality of life. The Morningness-Eveningness Questionnaire (MEQ) is a 19 items self-assessed questionnaire constructed to assess chronotype. A score below 42 indicates “evening type” and a score above 58 indicates “morning type”; and a score between 42 and 58 indicates “intermediate type” [54]. Sleep quality is assessed by the PSQI containing 11 self-reported items. These items are transformed into 7 “component scores” , and a “global score”. The components scores are “Subjective sleep quality (1)”, “Sleep latency (2)”, “Sleep duration (3)”, “Sleep efficiency (4)”, “Sleep disturbances (5)”, “Sleep medication (6)” and “Daytime dysfunction (7)”. A “Global Score” of 5 or above indicates poor sleep quality [55]. The System Usability Score (SUS) is used to evaluate the usability of the MDB system [56].

#### Biochemical assessments

The Dim Light Melatonin Onset (DLMO) will be determined by saliva sampling every 45 min in the evening from 5 h before expected bedtime until 1 h after expected bedtime at baseline and endpoint (6 samples at each assessment day). The patient will collect samples at home according to a delivered 1-page guideline. The important rule from this guideline is to wear orange goggles (provided by investigators) for the entire 6-h episode of saliva sampling (to prevent suppression of melatonin secretion by blue light). The samples will be refrigerated and kept frozen until the melatonin assay. All samples obtained from a single patient will be assayed in the same batch to avoid inter-assay variability. The DLMO, a marker of circadian phase, is determined as the time point where melatonin production rises [57] using the hockey-stick method [58]. Patient-reported sleep data is used to calculate sleep midpoint. From sleep midpoint and DLMO, we can calculate the Phase Angle Difference (PAD) as a measure of entrainment [59]. The normal value of PAD is 6 h [56]. We expect patients to have a phase delayed DLMO relative to sleep midpoint with a PAD of approximately 5 h.

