## Design

The trial protocol is reported according to the SPIRIT statement of randomized trials of nonpharmacologic treatment [47]. The trial is a four-week, randomized, controlled, single-blind, parallel-group trial with a balanced allocation ratio (1:1) of adult patients diagnosed with MDD. Patients will be randomized to either a) a *Standard group* consisting of electronic self-monitoring and usual care at an intensive outpatient service (IOS), or to b) a *CRT group* using the CRT method with electronic monitoring and usual care at the IOS. Patients are psychometrically assessed at baseline and after 4 weeks. The trial investigates the possible effect of CRT on depression. All patients will self-monitor with the MDB system and receive usual care at the IOS. The design of the control group (*Standard group*) was chosen based on the necessity for the intended sample at IOS to have access to qualified and adequate treatment. Thus, placebo treatment was not an option. As we were interested in the isolated effect of the CRT intervention, we opted that both study groups should use the MDB system and receive treatment at the IOS.

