**Fig. 1 Fig1:**
[figure not shown]
An example of a graphic presentation in the Monsenso Daybuilder System, that can be viewed simultaneously by the patient and the clinician. In this example only mood, sleep and activity are shown. Sleep is visualized as a blue ribbon with the lower border representing sleep-onset and the upper border wake-up time. Mood is shown as a red line with diamond symbols with scores from zero to 10 (10 = best). Activity (=Exercise) is shown as yellow dot symbols representing accumulated 24-h counts measured by a Fitbit charge HR bracelet

Morning self-assessments: sleep onset, wake-up time, sleep quality score, number of nighttime awakenings, unlimited qualitative description of their sleep episode, and morning depression severity.

Evening self-assessments: daytime naps with timing and duration of each nap, activity from the Fitbit (the Fitbit resets the activity count at midnight), medication compliance (yes or no), evening depression severity, depression severity as an average of the last 24 h, and unlimited qualitative description of zeitgeber strategies that they have been using for the last 24 h in order to keep a stable sleep-wake cycle (*CRT* group only). Regarding depression severity, patients are instructed to evaluate their depression based on the DSM-IV diagnostic items for MDD. These item descriptions are written on the interface next to the data entry tab: “depressed mood, diminished interest, significant weight or appetite changes, insomnia or hypersomnia, agitation or retardation, loss of energy or tiredness, feelings of worthlessness or guilt, difficulties in concentrate, and suicidal ideations”. All quantitative parameters are scored from zero to 10 (10 is best).

The Fitbit bracelet enables the collection of activity and heart rate. These will be investigated as a predictor for antidepressant response and as markers of the circadian rhythm.

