### Ranking of outcomes

The primary outcome is the change in interviewer rated levels of depression (blinded) measured by the Hamilton Depression Rating scale 17-item version. The secondary outcome is the change in self-assessed depression level based on the scores on the Major Depressive Inventory. The tertiary outcome is the change, in minutes, of the Phase Angle Difference (PAD) on the subset of patients assessed with Dim Light Melatonin Onset (DLMO).

Explorative outcomes are: (a) changes in quality of life based on changes on the WHO-5 wellbeing scale, (b) self-rated depression severity from the MDB system (c) self-rated sleep quality from the MDB system, (d) chronotype from the MEQ and, (e) sleep quality assessed by the Pittsburgh Sleep Quality Index, (f) Fitbit pulse and activity data.

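### The sleep midpoint in the tertiary outcome is self-reported by patients who know their arm and, in the CRT arm only, are coached on it, so arm-specific reporting error can enter PAD with no planned check

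*Protocol article*

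**What the plan says.** Under Biochemical assessments, the protocol article fixes the source of the midpoint: "Patient-reported sleep data is used to calculate sleep midpoint". It continues: "From sleep midpoint and DLMO, we can calculate the Phase Angle Difference (PAD) as a measure of entrainment". Under Ranking of outcomes: "The tertiary outcome is the change, in minutes, of the Phase Angle Difference (PAD) on the subset of patients" who have DLMO measured.

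The Design section calls the trial single-blind. The Blinding section names only the Hamilton rater as blinded. Patients receive an envelope stating their group (Allocation) and are told not to disclose it to the rater (Data collection).

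Both arms type sleep onset and wake-up time into the Monsenso Daybuilder (MDB) system each morning. The procedures for the CRT group add a module "using a graphical depiction of a manometer measuring day-to-day variation in sleep onset, and another manometer measuring changes in sleep midpoint". Under the same heading come weekday review of entries by the investigator, calls prompted by the triggers in Table 1, and weekly discussion of the graphs with a view to earlier sleep. One trigger reads: "Late sleep for 3 days – with sleep onset after midnight and wake up time after 9 am". The weekly calls listed for the Standard group cover system experience, suicidal ideation, side effects, worsening and data-entry compliance, but not sleep timing.

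On the bracelet, the article says: "The Fitbit bracelet enables the collection of activity and heart rate". The explorative outcomes include "Fitbit pulse and activity data". No use of the bracelet for the sleep midpoint is stated.

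**The concern.** PAD looks objective because one half of it is a hormone assay. The other half is a clock time supplied by an unblinded patient. In one arm, the intervention works directly on those clock times: it displays them as a gauge, reviews them on weekdays, calls the patient about some of them and discusses how to shift them. A CRT patient learns which entries look favourable, and a Standard patient gets much less of this. If that changes what patients type as well as how they sleep, the reporting part goes straight into the between-arm contrast in PAD.

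What is at stake is the meaning of the tertiary result. A PAD difference, or the lack of one, is meant to show whether CRT changed circadian alignment. As planned, nothing in the PAD analysis would show whether reporting behaviour contributed.

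**Working it through.** **Inputs.** From Sample size: CRT PAD goes from 5 h to 6 h and Standard PAD is unchanged, so the planned difference in change is 60 min; SD 80 min; alpha 0.05 (two-sided assumed); power 0.80; total 58. From Biochemical assessments: normal PAD 6 h, about 5 h expected when DLMO is delayed relative to sleep midpoint. The size of any reporting error is not in the document; I call it b and vary it.

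**Step 1: the plan's own figure.** For a two-sample t-test, the noncentral t calculation gives 29 per arm, total 58, power 0.801. The normal approximation gives 28 per arm, total 56. The stated 58 reproduces.

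**Step 2: sign of PAD.** A later DLMO is said to shorten PAD from 6 h to 5 h, so PAD = sleep midpoint − DLMO.

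**Step 3: how error passes through.** Midpoint = (onset + wake) / 2. If onset and wake are both reported x min earlier than true, the midpoint is x min earlier and PAD is x min smaller. An error that is the same in both arms, or the same at baseline and endpoint, cancels in the contrast of changes. So b is the between-arm difference in the change of the mean reporting error. The CRT cues run from baseline to endpoint, so such a difference could arise over that interval.

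**Step 4: size against the planned effect.** 15/60 = 25%; 30/60 = 50%.

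**Step 5: operating characteristics.** Standard error = 80 × √(2/29) ≈ 21.0 min. The noncentrality is (60 − b)/21.0 if the error opposes the effect, (60 + b)/21.0 if it adds to it, and b/21.0 if there is no true effect.

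| Assumed b (min) | Power, error opposes a true 60-min effect | Power, error adds to it | Rejection rate, no true effect |
|---|---|---|---|
| 0 | 80.1% | 80.1% | 5.0% |
| 10 | 64.8% | 90.6% | 7.5% |
| 15 | 55.8% | 93.9% | 10.8% |
| 20 | 46.5% | 96.3% | 15.5% |
| 30 | 28.9% | 98.8% | 28.9% |

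**Step 6: likely direction.** The late-sleep trigger and the coaching both favour earlier entries. Entries earlier than the truth shrink PAD in the CRT arm, against the hypothesised rise. The opposing column is therefore the more plausible one, if there is error at all.

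**The case against.** Several points on the other side are sound and limit the claim.

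- **The contrast between arms is partial.** The abstract says all participants can view their data graphically and have clinician contact, with a stable sleep-wake cycle as the aim. Standard patients also see their sleep ribbon and get weekly calls. What is specific to CRT is the manometers, the trigger calls and the coaching.
- **Most cues reward regularity, not earliness.** The manometers show variation and change, and only one of the five sleep triggers concerns late sleep. Smoothing entries reduces their spread but need not move the mean midpoint. The uniform earlier shift behind the 15 to 30 min range is an assumption.
- **A motive to avoid calls is conjecture.** The article presents access to clinicians as a benefit.
- **The source is inferred.** The article says patient-reported sleep data without naming MDB. MDB is the natural reading, because it collects onset and wake-up times and its manometer displays midpoint.
- **The bracelet is not a ready substitute.** Activity is described as a daily total typed in by the patient, from which rest onset cannot be derived. Pulse is a listed outcome but not a typed entry, so retrieval of device records is implied but not stated. The step goal and the call for missing activity entries appear under the CRT procedures, so wear may differ by arm.

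A reader might infer that misreporting does bias PAD, that a PAD result cannot be separated from reporting behaviour, or that the diary midpoint must be replaced. The article supports none of these. It shows a route for error, not error. Assayed DLMO timepoints are to be described in their own right and can be read beside PAD. Diary against device is a trade-off with losses on both sides.

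What survives is that the article fixes an unblinded self-report as half of this outcome, the intervention acts on that same quantity in one arm, and no check is tied to it. This is a stated choice, not a detail left to an analysis plan.

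**Conclusion.** The point holds as a risk to how the tertiary outcome can be interpreted. Arm-specific reporting error can enter PAD minute for minute. Its size is unknown. Under an assumed between-arm error of 15 to 30 min, it equals 25% to 50% of the planned change. Power falls from 80% to between 56% and 29% if the error opposes the effect; with no true effect, the false-positive rate rises from 5% to between 11% and 29%. These figures assume 29 per arm, SD 80 min, a two-sided test at 0.05, and a shift in the mean, not only in the spread. The likelier direction hides the sponsor's own expected effect; it is less likely to create a false claim of benefit. The consequence is confined to PAD in the DLMO subset and to other self-reported sleep timing. HAM-D17, rated blind, is not touched by this route.

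**What to change.** Keep the self-reported midpoint for the main PAD analysis, and name its source and the nights used. Then prespecify:

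1. A sensitivity analysis that recomputes PAD with a midpoint from the bracelet's time-stamped activity and heart-rate record on the nights around each saliva evening, in both arms, by one rule applied without knowledge of arm.
2. Self-reported minus device midpoint, by arm, at baseline and endpoint, with the number of nights that have usable wear.
3. The change in DLMO alone, by arm.
4. A reading rule: a PAD difference is interpreted as circadian only if these results agree with it.

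The cost is analysis wording and some data processing. Device rest onset is noisier in patients who lie awake, and some nights will lack wear, possibly unequally by arm. The analysis also depends on time-stamped device data being retrieved, which the article implies but does not state and which should be confirmed first. If only daily totals exist, items 1 and 2 are not possible. Item 3 should then be reported and PAD described as partly self-reported.

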### Ranking of outcomes

The primary outcome is the change in interviewer rated levels of depression (blinded) measured by the Hamilton Depression Rating scale 17-item version. The secondary outcome is the change in self-assessed depression level based on the scores on the Major Depressive Inventory. The tertiary outcome is the change, in minutes, of the Phase Angle Difference (PAD) on the subset of patients assessed with Dim Light Melatonin Onset (DLMO).

Explorative outcomes are: (a) changes in quality of life based on changes on the WHO-5 wellbeing scale, (b) self-rated depression severity from the MDB system (c) self-rated sleep quality from the MDB system, (d) chronotype from the MEQ and, (e) sleep quality assessed by the Pittsburgh Sleep Quality Index, (f) Fitbit pulse and activity data.

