**Methods:**

In this trial, we apply a new treatment intervention, named Circadian Reinforcement Therapy (CRT), to patients discharged from inpatient psychiatric wards. CRT consists of a specialized psychoeducation on the use of regular time signals (zeitgebers): daylight exposure, exercise, meals, and social contact. The aim is to supply stronger and correctly timed zeitgebers to the circadian system to prevent sleep drift and worsening of depression. The CRT is used in combination with an electronic self-monitoring system, the Monsenso Daybuilder System (MDB). By use of the MDB system, all patients self-monitor their sleep, depression level, and activity (from a Fitbit bracelet) daily. Participants can inspect all their data graphically on the MDB interface and will have clinician contact. The aim is to motivate patients to keep a stable sleep-wake cycle. In all, 130 patients referred to an outpatient service will be included. Depression rating is blinded. Patients will be randomized 1:1 to a *Standard group* or a *CRT group*. The intervention period is 4 weeks covering the transition phase from inpatient to outpatient care. The primary outcome is score change in interviewer rated levels of depression on the Hamilton Depression Rating Scale. A subset of patients will be assessed with salivary Dim Light Melatonin Onset (DLMO) as a validator of circadian timing. The trial was initiated in 2016 and will end in 2020.

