Sleep disturbances are present in 50–90% of patients with depression [39]. The biological basis for sleep disturbances in depressed patients are not fully elucidated, but there is evidence for a circadian component such as misaligned morning cortisol increase [40], diurnal variation in mood with evening improvement, staying up late [41], and even inappropriate light habits [42]. Forced changes in the timing of the sleep-wake cycle are often linked to corresponding changes in depression severity. Thus, a sleep-phase delay has been shown to worsen depression [43], and sleep phase advance and sleep deprivation have a well-established antidepressant effect [44, 45]. Furthermore, daytime naps induce hour-long mood drops in a large proportion of depressed patients [46]. Our usability study, using electronic monitoring that documented sleep patterns over a four-week period in patients recently discharged from a mental health hospital, found a day-to-day highly variable sleep-wake cycle with gradually delayed sleep and unstable mood [6].

Therefore, enforcement and timing of zeitgebers with a focus on the regulation of the sleep-wake cycle present itself as a possible new treatment method. In this study we will help patients to attain a time-structured environment with regularly timed zeitgeber stimuli: daylight exposure, exercise, meals, and social contact, to sustain a stable sleep cycle. We have coined this newly proposed intervention: Circadian Reinforcement Therapy (CRT).

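### PAD alone cannot tell an intended melatonin advance from the later sleep that CRT should prevent, and no named outcome measures sleep timing

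*Protocol article*

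**What the plan says.** Under Ranking of outcomes, the protocol article states: "The tertiary outcome is the change, in minutes, of the Phase Angle Difference (PAD) on the subset of patients" who have DLMO assessed. No direction of benefit is given there.

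Biochemical assessments describes the measure: "From sleep midpoint and DLMO, we can calculate the Phase Angle Difference (PAD) as a measure of entrainment". On its inputs it says "Patient-reported sleep data is used to calculate sleep midpoint". It gives a reference value, "The normal value of PAD is 6 h", and an expectation for this population: "We expect patients to have a phase delayed DLMO relative to sleep midpoint with a PAD of approximately 5 h". Sample size then assumes that the CRT group goes from 5 h to 6 h, which it treats as a return to normal. It assumes that the Standard group stays at 6 h. With an SD of 80 min, alpha 0.05 and power 0.80, it arrives at 58 patients.

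The rationale concerns sleep timing. The Methods part of the Abstract says: "The aim is to supply stronger and correctly timed zeitgebers to the circadian system to prevent sleep drift and worsening of depression". The section Sleep, circadian rhythms, and zeitgebers reports that the group's earlier study of recently discharged patients "found a day-to-day highly variable sleep-wake cycle with gradually delayed sleep and unstable mood". Procedures for the CRT group makes an earlier sleep period a topic of the weekly calls.

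Among the explorative outcomes, the sleep-related entries are "c) self-rated sleep quality from the MDB system", chronotype from the MEQ and sleep quality from the PSQI. Fitbit pulse and activity are also listed. Sleep onset, wake time, sleep midpoint and day-to-day variability are not. Yet sleep onset and wake time are entered every morning in both groups. Statistical methods plans a mixed model of the daily depression, activity and sleep data without saying which sleep variable. It also plans descriptive summaries of DLMO time points.

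**The concern.** PAD is a difference between two clock times, so either one can move it. Two changes that the trial most needs to tell apart push PAD the same way: an earlier DLMO, which is the hoped-for effect, and a later sleep midpoint, which is the drift seen after discharge. An earlier sleep midpoint, which CRT encourages, pushes PAD the other way unless DLMO moves at least as far.

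The reading of the tertiary result is at stake. A rise in PAD in one arm could be circadian correction or sleep drift. A null contrast could hide a DLMO advance under CRT that is offset by later sleep in the Standard group. A fall under CRT could accompany exactly the earlier sleep that the sessions aim for. The outcome list offers nothing to resolve this, because it names no measure of sleep timing. The mixed model could supply one, but its sleep variable is not named, so the choice among quality, duration and timing is open in this document.

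**Working it through.** **1. Sign of PAD.** No formula is printed. Biochemical assessments says that a DLMO late relative to sleep midpoint goes with a PAD of about 5 h instead of 6 h. A later DLMO shortens the interval only if

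PAD = sleep midpoint − DLMO, so change in PAD = change in midpoint − change in DLMO.

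**2. The plan's own figure.** Inputs from Sample size: CRT change 6 h − 5 h = +60 min, Standard change 0, SD 80 min, alpha 0.05 (taken as two-sided), power 0.80, allocation 1:1. The standardized difference is 60/80 = 0.75. The two-sample t calculation gives 28.9, so 29 per arm and 58 in total, with power 0.801. The normal approximation gives 28 per arm, 56 in total. The stated 58 is reproduced, with the contrast taken as a difference in change and 80 min as the SD of that change.

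**3. What moves PAD, from a baseline of 5 h (300 min).**

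| Sleep midpoint | DLMO | Change in PAD | New PAD |
|---|---|---|---|
| unchanged | 60 min earlier | 0 − (−60) = +60 | 6.0 h |
| 60 min later | unchanged | 60 − 0 = +60 | 6.0 h |
| 60 min later | 30 min later | 60 − 30 = +30 | 5.5 h |
| 60 min later | 60 min later | 60 − 60 = 0 | 5.0 h |
| 60 min earlier | 60 min earlier | −60 − (−60) = 0 | 5.0 h |
| 60 min earlier | 30 min earlier | −60 − (−30) = −30 | 4.5 h |
| 60 min earlier | unchanged | −60 − 0 = −60 | 4.0 h |

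The first two rows give the same score for opposite clinical stories. Later sleep raises PAD whenever DLMO is delayed less than sleep. Earlier sleep lowers PAD whenever DLMO advances less than sleep.

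**4. Illustration of the effect on power.** The documents give no drift in minutes and no DLMO data from the earlier study, so the drift below is an assumption, shown as a range. CRT gains 60 min as planned. The Standard midpoint drifts later by d min with DLMO fixed, so the contrast is 60 − d. With 29 per arm and SD 80 min, the noncentrality is (60 − d)/80 × √(29/2), on 56 degrees of freedom.

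| Assumed drift d | Contrast | Power |
|---|---|---|
| 0 min | 60 min | 0.80 |
| 15 min | 45 min | 0.56 |
| 30 min | 30 min | 0.29 |
| 45 min | 15 min | 0.11 |
| 60 min | 0 min | 0.05 |

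**5. Baseline of the Standard group.** Biochemical assessments expects patients at about 5 h. Sample size has the Standard group at 6 h throughout. On those assumptions both arms end at 6 h, so an endpoint comparison would have an expected difference of 0. The 58 follows only from comparing changes (60 against 0 min). The starting value does not alter the power table, which is on change. It does alter the label: 30 min of drift takes a Standard patient from 5 h to 5.5 h (towards normal) but from 6 h to 6.5 h (away from it).

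**The case against.** The strongest reply is that the mis-scoring is conditional. PAD does not change when sleep and DLMO shift together, and the protocol's own account has timed zeitgebers acting on the circadian clock. In a patient whose sleep advances while DLMO stays put, that mechanism has not worked, so a lower PAD is not plainly an error. PAD is also offered as a measure of entrainment, not of drift, and misalignment between rhythms is a stated part of the rationale. All of this stands. It defends PAD as an outcome, but does not make its sign interpretable without its two components.

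A reader might infer that an unchanged Standard PAD contradicts the drift hypothesis. It does not: equal delay in sleep and DLMO leaves PAD where it was.

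A reader might also infer that the mechanism goes untested. The documents do not support that. Daily sleep data enter a mixed model, DLMO time points are summarized, Fitbit data are to be examined as circadian markers, and PAD itself contains the sleep midpoint. Which sleep variables are modelled is detail that an article may leave to a fuller document. What remains is narrower: the outcome list itself names sleep quality and chronotype but not timing or regularity.

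Finally, the stated objective is to prevent worsening of depression, and the HAM-D17 and MDI outcomes address it directly. That limits the weight of this point.

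**Conclusion.** The point holds in a limited form. On the protocol's own reference values, PAD alone is directionally ambiguous: an increase of 60 min from 5 h can come from the intended DLMO advance or from an equal delay in sleep. The tertiary result therefore cannot by itself separate benefit from drift. It would go too far to say that PAD scores drift as normalization outright, since that requires DLMO to be fixed or to lag behind sleep and the patient to start below 6 h.

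The power figures, 0.80 falling to 0.56, 0.29, 0.11 and 0.05, show sensitivity only. They rest on an assumed Standard-group drift with DLMO fixed and the full planned gain under CRT. The stated 58 is arithmetically sound.

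The outcome list names no sleep-timing or regularity measure, although the data are collected daily. The Standard-group PAD of 6 h also does not agree with the 5 h expected in patients. The change is cheap and worth making, because it decides what the trial can conclude about its rationale. The primary and secondary outcomes are not affected.

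**What to change.** 1. State the PAD formula and its sign. Beside PAD, compare between arms the change in DLMO clock time and the change in sleep-midpoint clock time in the saliva subset, and interpret PAD only together with both.
2. Name as explorative or supportive outcomes, in all patients, the 4-week slope of sleep midpoint and its day-to-day variability. Derive both from the daily sleep onset and wake times, and analyse the slope in the mixed model already planned.
3. Reconcile the Standard-group PAD of 6 h in Sample size with the roughly 5 h in Biochemical assessments, and say that the calculation compares changes.

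No new data or procedures are needed. The costs should be stated openly. There would be one or two more outcomes to report. They would be named after enrolment began, with 64 patients included by April 2019 and investigators able to see the self-monitoring data, so the date of the decision should be recorded. Sleep timing is also unblinded self-report of behaviour that CRT coaches, and only CRT patients see the displays of sleep onset and midpoint variation. The sleep-timing results should therefore be supportive, not confirmatory. DLMO is less exposed to that reporting bias, which is a further reason to show it separately.
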